### Interventions

2.7

#### Control group

2.7.1

Sleep hygiene education: Actively communicate with the patient to understand the causes of insomnia, provide targeted guidance and explanations to alleviate negative emotions, and provide a sleep education manual. This includes informing patients about the importance of sleep, guiding them to create a good sleep environment, changing poor sleep habits, and engaging in regular physical exercise. The recommended exercise regimen consists of running (moderate-intensity aerobic activity) with a frequency of three sessions per week (24). Follow-up will be conducted regularly using ASHS, PSQI, ASWS, CDI, and BDI scales to assess sleep and psychological health. If the patient shows signs of depression, appropriate treatment will be provided.

#### AA group

2.7.2

In the AA group, AA will be applied in addition to sleep hygiene education. Points: Shenmen (TF4, located in the triangular fossa, above the division of the ear lobe), Subcortex (AT4, on the inner side of the ear), Endocrine (CO18, anterior lower part of the ear canal), Liver (CO12, behind the lower part of the ear), Heart (CO15, central part of the ear), Kidney (CO10, below the upper and lower branches of the ear lobe) (**Figure 3**). These points will be carefully located according to the guidelines in the “Illustrated Ear Acupuncture” by Shanghai Science and Technology Publishing House. After evaluation, the most sensitive areas will be treated with ear acupressure beans. Each session will treat one ear, with changes to the other ear every 3 days. Patients will be instructed to press the acupressure beans 3–5 times per day, 1–2 minutes per session. The treatment will last for 8 weeks, followed by follow-ups at 3 months and 6 months.

**Figure 3 f3:**
[figure not shown]
The accurate positioning of auricular points.

#### SAA group

2.7.3

In the SAA group, SAA will be applied in addition to sleep hygiene education. The same points as in the AA group will be selected, but adhesive tapes without seeds will be placed on the ear. To reduce intergroup differences and improve the effectiveness of the blinded method, the SAA group will also be required to press the ear patches according to uniform instructions to maintain consistency with the AA group’s operating procedures. This will prevent patients from easily guessing the groupings and ensure similarity in the operating experience between the two groups during the intervention. At the end of the study, patients will receive the same AA treatment as the ear acupressure group.

In addition, to minimize dropout rates and enhance participant adherence, researchers will engage with participants during each replacement of the ear acupressure beans. Participants will be reminded to apply pressure according to the prescribed frequency and duration, and to regularly monitor the placement and condition of the ear acupressure beans. These measures aim to encourage continued compliance with the study protocol.

### Outcome assessment

2.8

#### Primary outcome

2.8.1

PSQI: The Chinese version of the PSQI will be used for assessment (25, 26), which has been proven to be highly reliable and effective in evaluating the sleep quality of Chinese adolescents (27).The PSQI covers seven key dimensions: sleep quality, sleep latency, sleep duration, sleep efficiency, sleep disturbances, use of sleep medication, and daytime dysfunction. The total score ranges from 0 to 21, with higher scores indicating poorer sleep quality. A PSQI score > 7 is used as the cutoff for sleep quality problems.

BDI: A 21-item scale designed to assess core depressive symptoms, evaluating clinical manifestations over the past two weeks to determine depression severity, with total scores ranging from 0 to 63. For non-clinical adolescent populations, a BDI score ≥20 indicates the presence of depressive symptoms (28, 29).

#### Secondary outcome

2.8.2

ASHS: A self-report measure assessing adolescents’ pre-sleep behavioral habits over the past month, including typical sleep routines and conditions, demonstrating robust psychometric properties (30). The scale consists of 28 items divided into 9 categories, with higher scores indicating better sleep hygiene. Categories include: Physiological domain (e.g., “I feel hungry when I go to bed”), Cognitive domain (e.g., “I go to bed thinking about things I need to do”), Emotional domain (e.g., “I feel anxious when I go to bed”), Sleep environment (e.g., “I fall asleep while watching TV”), Daytime sleep (e.g., “I nap for more than 1 hour during the day”), Substances (e.g., “I drink beer or other alcoholic beverages after 6 PM”), Bedtime (e.g., “I have a consistent bedtime”), Sleep stability (e.g., “I stay up later on weekends than my usual bedtime”), Bed/room sharing (e.g., “I sleep alone”)

CDI: CDI developed for children aged 6–16 years demonstrates good reliability and validity in Chinese pediatric populations (31), with participants selecting items that best describe their feelings over the past two weeks. The CDI consisted of 27 items divided into five dimensions: Anhedonia, Negative Mood, Negative Self-Esteem, Ineffectiveness, and Interpersonal Problem. Participants are asked to choose the item that best describes how they have felt in the past two weeks. Responses ranged from 0 to 2, indicating “often”, “occasionally”, and “always”, representing the frequency of occurrence, for a total score of 54. Lower scores indicate fewer depressive symptoms.

ASWS: The adolescent sleep quality self-report scale, clinically validated for reliability and validity (32), comprises 28 items designed to assess sleep quality in youth aged 12 to 18 years. Respondents are asked to rate the frequency of their sleep behaviors during the past month using a 6-point scale (ranging from “always” to “never”). Adolescent sleep is assessed across five behavioral dimensions: Bedtime (5 items), Sleep onset (6 items), Sleep maintenance (6 items), Sleep resumption (6 items), Waking up refreshed (5 items). An average subscale score for each dimension and a total sleep quality score (ASWS total score) can be obtained, with scores ranging from 1 to 6. Higher scores indicate better sleep quality.

ASLEC: A self-rating scale for negative life events specifically developed for adolescents by Chinese experts. The ASLEC assesses life events in the past six months at baseline, covering 27 items across six domains of negative life events in adolescents: interpersonal relationships, academic pressure, family conflicts, and health. The scale has sufficient test-retest reliability and concurrent validity, with total scores ranging from 0 to 108 (33).

### Statistical analysis

2.9

Statistical analyses will be performed using SPSS 25.0 (SPSS, Chicago, IL, USA). The incidence of adolescent depression will be calculated based on the Beck Depression Inventory (BDI) thresholds established in prior studies. Continuous variables will be presented as mean ± standard deviation, while categorical data will be expressed as percentages or proportions. A p-value <0.05 will be considered statistically significant for intergroup differences, and p<0.01 will indicate highly significant differences.

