**Methods:**

This study is a single-center, double-blind, randomized controlled trial conducted in Nanjing, China. Participants are students from junior and senior high schools in Nanjing. A multi-stage stratified cluster sampling method is used to recruit students from 7th and 8th grades (junior high) and 10th and 11th grades (senior high). Baseline data will be collected using the Chinese version of the Pittsburgh Sleep Quality Index (PSQI), Beck Depression Inventory (BDI), Adolescent Sleep Hygiene Scale (ASHS), Children’s Depression Inventory (CDI), Adolescent Self-rating Life Events Checklist (ASLEC) and Adolescent Sleep-Wake Scale (ASWS), and insomnia patients will be identified. Adolescents who met the inclusion and exclusion criteria and whose guardians signed informed consent forms will be enrolled in the study. They will be randomly assigned to one of three groups: AA group, sham auricular acupressure (SAA) group, and control group. The treatment lasted for 8 weeks, with follow-up assessments at 3 and 6 months post-treatment. The primary outcome measures are PSQI and BDI scores, while secondary outcome measures included ASHS, CDI, ASLEC, and ASWS scores.

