### Sample size

2.3

Based on the type of study, the sample size is calculated using PASS 15.0 software. The PSQI score of insomnia patients is chosen as the outcome measure. Based on literature and preliminary experimental results, the average PSQI score for the drug control group is 10.76 ± 3.32, and it is expected that the PSQI score in the insomnia group will decrease by 2.63 points. An effect size of 0.8 is used, with α = 0.05 and power = 0.9. The calculated sample size for each group (AA group, SAA group, control group) is N1 = N2 = N3 = 52. Considering a 20% dropout rate, the total sample size required is N1 = N2 = N3 = 65. According to previous reports [5], the prevalence of insomnia in adolescents is 20%, so the sample population is (N1 + N2 + N3) ÷ 20% = 975, then the sample population should be more than 975.

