### Randomization

2.5

After screening based on the inclusion and exclusion criteria, eligible adolescent insomnia patients will be randomly assigned in a 1:1:1 ratio to the AA group, SAA group, or control group. The randomization sequence will be generated by researchers who are not involved in the trial implementation or statistical analysis using SPSS 25.0 software. The sequence will be hidden using the envelope method, and each envelope will contain the randomization order for patient allocation. A designated person will be responsible for patient inclusion, and patients will receive the corresponding envelope in the order of enrollment.

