#### Intergroup comparison methods

2.9.1

For normally distributed measurement data meeting the assumptions of parametric tests, within-group pre- and post-treatment comparisons will be conducted using paired-sample t-tests. Intergroup comparisons will employ one-way ANOVA. Non-normally distributed measurement data will be analyzed using nonparametric rank-sum tests, and categorical data will be assessed via chi-square tests or Fisher’s exact probability test. These comparisons will evaluate the therapeutic effects of auricular acupressure.

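### PSQI and BDI are joint primaries judged at an unadjusted p<0.05 with no deciding visit, contrast or both-must-succeed rule, so the false-positive risk exceeds 5% if either can succeed

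*Protocol article*

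**What the plan says.** - **Outcomes.** The abstract states: "The primary outcome measures are PSQI and BDI scores, while secondary outcome measures included ASHS, CDI, ASLEC, and ASWS scores". Section 2.8.1 lists PSQI and BDI together under the primary outcome, with no order between them. Section 2.9 also turns BDI into a depression incidence by means of a threshold.
- **Arms.** Section 2.5 has participants "randomly assigned in a 1:1:1 ratio to the AA group, SAA group, or control group".
- **Visits.** The abstract says: "The treatment lasted for 8 weeks, with follow-up assessments at 3 and 6 months post-treatment". Section 2.7.2 agrees. The text calls none of these visits primary.
- **Tests.** Section 2.9.1: "Intergroup comparisons will employ one-way ANOVA", with rank-sum, chi-square or Fisher tests where appropriate. Section 2.9.2 adds repeated-measures ANOVA or mixed models, looking at time and the time-by-group interaction. No pairwise contrast or post-hoc procedure is named.
- **Decision rule.** Section 2.9: "A p-value <0.05 will be considered statistically significant for intergroup differences, and p<0.01 will indicate highly significant differences".
- **Sizing.** Section 2.3: "The PSQI score of insomnia patients is chosen as the outcome measure". It uses alpha 0.05 and describes no adjustment; BDI plays no part.

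**The concern.** A single 5% threshold gives a 5% error rate for one test. Here it is applied to two outcomes that each carry primary status, at up to three visits, and the reader cannot tell which result settles the trial. Efficacy could be claimed on whichever primary, at whichever visit, crosses 0.05.

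The missing contrast is a separate weakness. A three-group F test can be significant because SAA differs from control, so it cannot by itself show that AA beats sham. If the reader turns to AA v control, the comparison is with an arm that gets sleep hygiene education and no tape (section 2.7.1). The masking measures in section 2.6 concern AA and SAA only, and the Discussion concedes that outcomes are self-reported. The contrast most open to expectation effects could therefore carry the conclusion.

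**Working it through.** **1. The plan's own figure.** Inputs from section 2.3: SD 3.32, difference 2.63, effect size 0.8, alpha 0.05, power 0.9. The ratio is 2.63/3.32 = 0.792, in line with 0.8.

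Two-sample formula, two-sided: n = 2(z₁₋α/₂ + z₁₋β)²/d².
- d = 0.8: 2(1.960 + 1.282)²/0.64 = 32.8, so 33 per arm.
- d = 0.792: 33.5, so 34 per arm.
- Exact t: 34 and 35.

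The stated 52 is not reproduced. The later steps are: 52/0.8 = 65, and 3 × 65/0.20 = 975. Some unstated adjustments come close to 52, for example alpha/6 by exact t (50–51). Section 2.3 describes none, so 52 is not evidence that multiplicity was handled.

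**2. Independent tests, as a reference.** The chance of at least one false positive is 1 − 0.95^m.

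| Tests | m | Chance |
|---|---|---|
| One omnibus test per primary | 2 | 9.75% |
| Omnibus, 2 outcomes × 3 visits | 6 | 26.5% |
| AA v SAA and AA v control, 2 × 3 | 12 | 46.0% |
| All pairwise, 2 × 3 | 18 | 60.3% |

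**3. Correlated tests.** Null trials were simulated with 52 per arm, normal data and 20,000 trials per setting. Correlations were 0.3, 0.5, 0.7 and 0.9 between visits, and 0.3, 0.5 and 0.7 between PSQI and BDI. **These are assumptions.** Sidedness is not stated; two-sided 0.05 was used.

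| Reading | Chance of at least one p<0.05 | Prescribed in 2.9.1? |
|---|---|---|
| Omnibus, one visit, 2 outcomes | 8.3–9.8% | Test yes; visit not named |
| Omnibus, three visits, 2 outcomes | 14.2–24.7% | Test yes; use at each visit is one reading |
| 12 AA contrasts, unadjusted | 23.9–41.1% | No |
| All 18 pairwise, unadjusted | about 30–51% | No |

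The low end of each multi-visit range belongs to the highest correlations. Tests of BDI incidence and of the time-by-group interaction are not counted.

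**4. After the fix.** One contrast, one visit per outcome, 0.025 for each primary: familywise error is at most 0.025 + 0.025 = 5%. The normal formula gives 2(2.241 + 1.282)²/0.64 = 38.8, so 39 per arm (40 for d = 0.792). Exact t gives 41 for either d. With 52 completers per arm, power is 96.3% (d = 0.8) or 96.0% (d = 0.792).

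**The case against.** **No pairwise test is prescribed.** A reader might infer that any one of 18 pairwise results would support a positive claim, and hence that the error rate is 40–50%. The documents do not support this. Section 2.9.1 prescribes a three-group ANOVA. With exactly three groups, pairwise tests made only after a significant F hold the nominal level for that outcome and visit, so three arms need not add inflation. Six of the 18 comparisons are SAA v control and cannot support a claim for AA. The pairwise figures therefore depend on an unstated procedure and are not the lead result.

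**Two-sided counts include results against AA.** This is true. Counting only results that favour AA over the 12 AA contrasts gives about 12–22% in null trials, or 6–11% if gated by the F test. The matching benchmark for a single test is 2.5%, so the excess remains.

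**The success rule is not stated.** If both primaries had to succeed, having two outcomes would not inflate the error. No such rule appears, and treating insomnia and preventing depression read as two aims, each of which could be claimed separately.

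**Alpha allocation can be left to an analysis plan.** In part. A post-hoc procedure often is, and the schedule figure is not shown. But the article is not silent: it fixes two primaries and one unadjusted threshold with a second tier below it. A later adjustment would have to override section 2.9.

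**Conclusion.** The point stands in a limited form. If either primary can succeed, the rule in section 2.9 does not hold a 5% error rate: it is about 8–10% on the mildest reading, just under double the nominal level, and about 14–25% if omnibus tests are read at every visit. To say that the rate far exceeds 5% is fair for the per-visit reading and too strong for the mildest.

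The higher figures, about 24–41% and 30–51%, apply only if unadjusted pairwise tests follow. The correlated figures all rest on assumed correlations, 52 per arm and normal data. The absence of a named contrast does not depend on those assumptions: the F test as written cannot answer whether AA beats sham.

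**What to change.** In sections 2.8.1 and 2.9:

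1. Name AA v SAA as the primary contrast, at one stated visit for each of PSQI and BDI.
2. Test the two at 0.025 each, or with Holm.
3. Treat all other visits, contrasts and scales as secondary, reported as estimates with 95% confidence intervals.

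Two alternatives are acceptable: a fixed sequence at 0.05 with PSQI first and then BDI, or an explicit rule that both must reach 0.05. BDI need not lose primary status, which matters because preventing depression is a stated aim. Removing the p<0.01 tier would be a matter of style.

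**Cost.** The threshold becomes slightly stricter: about 41 per arm in place of 34–35 by exact t, within the planned 52, so no extra participants are needed. The 96% power holds for the stated PSQI effect; no BDI effect is given, so power for BDI cannot be stated. The trial is registered and ethics-approved (section 2.4), so the change should be made as a documented amendment before outcome data are examined by arm.

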#### Intergroup comparison methods

2.9.1

For normally distributed measurement data meeting the assumptions of parametric tests, within-group pre- and post-treatment comparisons will be conducted using paired-sample t-tests. Intergroup comparisons will employ one-way ANOVA. Non-normally distributed measurement data will be analyzed using nonparametric rank-sum tests, and categorical data will be assessed via chi-square tests or Fisher’s exact probability test. These comparisons will evaluate the therapeutic effects of auricular acupressure.

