#### Multi-timepoint data analysis

2.9.2

For repeated-measures data satisfying the sphericity assumption, repeated-measures ANOVA will be applied. If the sphericity assumption is violated, Greenhouse-Geisser correction or multivariate ANOVA will be used. This analysis will examine the main effect of time on outcome measures and potential time-by-group interactions.

For non-normally distributed data or datasets with significant missing values across timepoints, mixed-effects models will be employed. These models accommodate unbalanced data and missing values while accounting for intra-individual correlations.

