#### Missing data handling and dropout analysis

2.9.3

Missing Data: Multiple imputation will be used to address missing data, leveraging intervariable correlations to generate plausible values and enhance result accuracy.

Dropout Analysis: The primary analysis will follow the per-protocol approach, including only subjects who adhered strictly to the study protocol. As a supplementary strategy, intention-to-treat (ITT) analysis will include all randomized participants regardless of protocol deviations or dropout status, preserving randomization integrity and minimizing selection bias. Additionally, baseline characteristics (e.g., age, sex, initial depression scores) of dropouts versus completers will be compared using chi-square or t-tests to assess systematic bias. Significant differences will prompt covariate adjustment in regression models.

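### Within-arm paired t-tests count as evidence that auricular acupressure works, and the between-arm ANOVA is neither baseline-adjusted nor fixed in advance

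*Protocol article*

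**What the plan says.** Section 2.9.1 gives the tests for measurement data: "within-group pre- and post-treatment comparisons will be conducted using paired-sample t-tests. Intergroup comparisons will employ one-way ANOVA". If the data are not normal, "Non-normally distributed measurement data will be analyzed using nonparametric rank-sum tests". The section closes with the purpose of all of these: "These comparisons will evaluate the therapeutic effects of auricular acupressure". It names no covariate and does not say whether the ANOVA uses post-treatment or change scores.

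Section 2.9.2 adds repeated-measures ANOVA: "This analysis will examine the main effect of time on outcome measures and potential time-by-group interactions". It then sets two switches: "If the sphericity assumption is violated, Greenhouse-Geisser correction or multivariate ANOVA will be used", and "For non-normally distributed data or datasets with significant missing values across timepoints, mixed-effects models will be employed".

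The only covariate rule is in section 2.9.3, after a comparison of dropouts with completers: "Significant differences will prompt covariate adjustment in regression models".

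Four facts elsewhere bear on this:
- Section 2.2.1 requires a PSQI above 7 for entry, and section 2.8.1 makes PSQI a primary outcome.
- The abstract has the baseline questionnaires, PSQI and BDI among them, identify the insomnia cases. The selecting score therefore appears to be the baseline score.
- Sections 2.7.1 to 2.7.3 give sleep hygiene education to all three arms.
- No section says which test is primary for PSQI or BDI.

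**The concern.** A paired t-test within the AA arm asks whether scores changed, not whether AA changed them. Three things other than AA can lower PSQI here: regression to the mean after selection on a high score, natural course, and the sleep hygiene education common to all arms. Only the contrast between arms removes them. Yet section 2.9.1 gives the within-arm tests the same job as the between-arm test, and nothing labels them descriptive. The main effect of time in section 2.9.2 averages over arms and carries the same artefact. A report could truthfully state a significant improvement with AA, follow the plan, and say nothing about AA.

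Two lesser weaknesses sit beside this. The stated between-arm test makes no use of baseline PSQI or BDI as a covariate, although both are collected. And several tests are available for one primary outcome, chosen after the data are seen by rules that set no threshold for normality or for how much missingness is significant, and that leave open whether a sphericity failure leads to Greenhouse-Geisser or to multivariate ANOVA.

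**Working it through.** **Plan's figures used.** Section 2.3 gives 52 evaluable per arm, SD 3.32, an expected difference of 2.63 points and 20% prevalence ("the prevalence of insomnia in adolescents is 20" percent). Its later steps reproduce: 52/(1 − 0.20) = 65 per arm, and 3 × 65/0.20 = 975. The 52 itself does not follow from the stated inputs (a two-group, two-sided calculation gives 33 to 35). That is a separate matter, and 52 is taken here as given.

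**1. Fall in PSQI with no treatment effect.** Assumptions: PSQI is normal in the screened population, 20% of pupils exceed 7, SD is 2.5 to 3.32 and retest correlation ρ is 0.5 to 0.8. The documents give neither the population SD nor ρ; the top of the SD range is the protocol's 3.32.

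- Cut-point: z = 0.8416. Mean excess of the selected pupils: λ = φ(z)/0.20 = 1.40 SD above the population mean.
- Expected fall on retest: (1 − ρ) × 1.40 × SD.
- Smallest: 0.2 × 1.40 × 2.5 = 0.70 points. Largest: 0.5 × 1.40 × 3.32 = 2.32 points.
- Against the planned effect: 0.70/2.63 = 27% and 2.32/2.63 = 88%.

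**2. How often the paired t-test is significant under no effect, n = 52.** In the selected group the baseline variance is (1 + zλ − λ²) = 0.219 SD². The change score has variance [(1 − ρ)² × 0.219 + (1 − ρ²)] SD². Population SD cancels in the ratio of mean change to its SD, so only ρ matters:

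| ρ | mean fall / SD of change | × √52 | rejection (simulated) |
|---|---|---|---|
| 0.5 | 0.700/0.897 = 0.780 | 5.63 | nearly 100% |
| 0.6 | 0.560/0.822 = 0.682 | 4.91 | over 99% |
| 0.7 | 0.420/0.728 = 0.577 | 4.16 | about 98% |
| 0.8 | 0.280/0.607 = 0.461 | 3.32 | about 90% |

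In the same simulations (4,000 runs per setting), all three arms were significant together in about 73% to nearly 100% of trials. One-way ANOVA on post-treatment scores rejected in 4.4% to 6.2%, which is its nominal level.

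**3. Precision of the between-arm test.** With baseline-outcome correlation r among enrolled pupils, adjustment multiplies residual variance by 1 − r²: 0.91, 0.75 and 0.64 at r = 0.3, 0.5 and 0.6, a cut of 9%, 25% and 36%. This r is assumed. It is not the same quantity as ρ, because selecting only high scorers narrows the baseline range and lowers the correlation. In the model above, ρ of 0.5 to 0.8 becomes ρ√0.219/√(0.219ρ² + 1 − ρ²) = 0.26 to 0.53 among those enrolled, so r near 0.6 is optimistic.

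Power for one pair of arms, two-sided 0.05, is Φ(Δ/SE − 1.96), with unadjusted SE = 3.32 × √(2/52) = 0.651. Adjustment multiplies SE by √(1 − r²):

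| Δ (PSQI points) | unadjusted | r = 0.3 | r = 0.5 | r = 0.6 |
|---|---|---|---|---|
| 2.63 | 98.1% | 98.9% | 99.7% | 99.9% |
| 1.5 | 63.5% | 67.5% | 75.8% | 82.1% |

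**4. The covariate rule.** It fires when dropouts differ from completers. That comparison pools over arms. A baseline score can predict the outcome strongly, and so be worth adjusting for, with no such difference. The rule therefore does not serve between-arm precision.

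**The case against.** Section 2.9.1 is headed as intergroup methods, section 2.9 attaches its significance level to differences between groups, and section 2.9.2 tests a time-by-group interaction. A fair reader could say that efficacy rests on the between-arm results, with paired tests as customary extras. That softens the point but does not remove it: the sentence assigning the purpose follows both tests and excludes neither.

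Several stronger readings are tempting, and the documents do not support them:
- That the whole efficacy analysis credits regression to the mean as benefit. Randomisation shares the fall across arms, and the ANOVA keeps its error rate.
- That baseline is thrown away. The paired tests use it, and so does the time-by-group interaction if baseline is one of its timepoints. What is absent is baseline as a covariate.
- That sections 2.9.1 and 2.9.2 contradict each other on non-normal data. They can be read as covering single comparisons and multi-timepoint data respectively.
- That repeated-measures ANOVA will simply drop the planned 20% of dropouts. Section 2.9.2 moves to mixed models when missingness is significant, and section 2.9.3 plans multiple imputation.
- That the Greenhouse-Geisser correction is itself a fault. It is routine; the open choice beside it is the weakness.

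The regression model is also simplified. It selects on a single PSQI score, whereas entry also needs an ICSD-3 diagnosis with more than three months of symptoms. Its selected mean of 8.4 to 8.85 lies below the 10.76 in section 2.3, though that figure belongs to a drug control group that this trial does not have. Finally, a separate analysis plan may settle the model. But the methods questioned here are stated in the article, not left open for it.

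**Conclusion.** The point holds for the within-arm tests and, more mildly, for the between-arm analysis. Used as the article states, the paired t-tests would be significant in about 90% to nearly 100% of trials with no AA effect, on an expected fall of 0.7 to 2.3 PSQI points. This rests on 20% of pupils exceeding 7 and on the assumed SD and retest correlation, and it leaves out any benefit from sleep hygiene education, which would add to the fall. It applies directly to PSQI. Pupils are not selected on BDI, so for that outcome the artefact is only indirect.

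The between-arm ANOVA is valid but less precise than the collected data allow. The loss is negligible if the true difference is 2.63 points and becomes material at smaller ones. The data-driven choice of test is a weakness of prespecification; its effect on the error rate cannot be computed from the documents. This should be corrected, but it does not invalidate the randomised comparison.

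**What to change.** For each primary outcome, name one between-arm model in advance: either ANCOVA with baseline score as covariate, or a mixed model for repeated measures with arm, visit, arm-by-visit and baseline score.

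- Base efficacy conclusions only on that model's between-arm contrasts, and reword the closing sentence of section 2.9.1 to say so.
- Report within-arm changes descriptively (mean change with SD), without p-values.
- Keep rank-based analyses as sensitivity only, so that normality, sphericity and missingness checks no longer choose the primary test.
- Adjust for baseline score whatever the dropout-versus-completer comparison shows.

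The cost is a change of wording before the data are analysed. No further data are needed, and SPSS, already named in section 2.9, fits both models.

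### The only clearly named between-group test, a three-arm one-way ANOVA, cannot show that AA is better than sham, and no AA versus SAA contrast is named

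*Protocol article*

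**What the plan says.** Section 2.9.1 (Intergroup comparison methods) gives paired t-tests for change within a group and, between groups, "Intergroup comparisons will employ one-way ANOVA". Rank-sum tests are named for non-normal data and chi-square or Fisher tests for categorical data, without saying how many arms enter each. The section closes: "These comparisons will evaluate the therapeutic effects of auricular acupressure". Section 2.9 sets p<0.05 for differences between groups.

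Section 2.9.2 (Multi-timepoint data analysis) adds repeated-measures ANOVA: "This analysis will examine the main effect of time on outcome measures and potential time-by-group interactions".

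Neither section names a pair of arms, a follow-up test or an order of comparisons. The independent t-tests in section 2.9.4 concern factors associated with depression, not treatment arms.

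The arms differ as follows:

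- Control (2.7.1) is described with education only: "Sleep hygiene education: Actively communicate with the patient to understand the causes of insomnia, provide targeted guidance".
- AA and SAA (2.7.2, 2.7.3) both add ear tape and pressing instructions to that education; SAA has no seeds.
- To support adherence, "researchers will engage with participants during each replacement of the ear acupressure beans" (2.7.3).
- The masking steps in section 2.6 cover only AA and SAA, although the same section says that participants stay blinded.

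**The concern.** With three arms, the F test asks whether all three means are equal. The clinical question has at least two parts: whether AA is better than sham, and whether the AA package is better than education alone. The F test answers neither. It rejects for any departure from equality, including the one in which AA and SAA do equally well and both beat control.

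That pattern is plausible here without any specific effect of the seeds. Both taped arms have something applied to the ear, a daily task and regular researcher contact, none of which is described for control. The outcomes are self-reported, as the Discussion acknowledges.

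If the plan is followed as written, a significant difference between groups could be reported as a therapeutic effect of AA when the data show only that taped adolescents did better than untaped ones. This is not a multiplicity problem. It arises with one outcome, one visit and an exact 5% test, and a smaller alpha does not remove it.

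**Working it through.** **Inputs.** Section 2.3 gives "An effect size of 0.8 is used, with α = 0.05 and power = 0.9". Its reference PSQI mean is 10.76 with SD 3.32, its planned fall is 2.63 points, and it sets 52 per arm before dropout and 65 after 20% dropout. Section 2.5 gives 1:1:1 allocation. The size of a benefit shared by both taped arms is not in the document, so it is an assumption and is shown as a range.

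**The plan's own figures.** 2.63 / 3.32 = 0.79, in line with the stated 0.8. The steps 52 / 0.8 = 65 and (3 × 65) / 0.20 = 975 reproduce. The 52 does not follow from the stated inputs. At 90% power and two-sided 0.05, a two-arm t-test at 0.8 SD needs 34 per arm, and the three-arm F test needs 31 (one arm different) or 41 (equally spaced means). That is a separate matter. Both 52 and 65 are used below as given.

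**Rejection by ANOVA when AA = SAA.** In SD units let the means be (−d, −d, 0). The grand mean is −2d/3, so the squared deviations sum to d²/9 + d²/9 + 4d²/9 = 2d²/3, and the noncentrality is λ = n × 2d²/3. For n = 52 and d = 0.4, λ = 52 × 2 × 0.16 / 3 = 5.55. The critical value of F(2, 153) is 3.06 and the probability of rejection is 54%. With n = 65 the critical value of F(2, 192) is 3.04.

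| Shared benefit d (SD) | PSQI points (d × 3.32) | ANOVA rejects, 52 per arm | ANOVA rejects, 65 per arm | AA v SAA t-test rejects |
|---|---|---|---|---|
| 0.2 | 0.66 | 17% | 20% | 5% |
| 0.3 | 1.00 | 33% | 40% | 5% |
| 0.4 | 1.33 | 54% | 64% | 5% |
| 0.5 | 1.66 | 75% | 84% | 5% |
| 0.8 | 2.66 | 99% | 99.8% | 5% |

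Simulation of 20,000 trials per setting at 0.4, 0.5 and 0.79 SD agreed with the noncentral F. For means (−d, 0, 0), where only AA works, the squared deviations again sum to 2d²/3. The F test therefore has exactly the same power for that pattern as for the one in which AA equals sham, and it cannot tell them apart.

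**Time-by-group interaction.** With four time points, AA = SAA, 52 per arm and an assumed within-person correlation of 0.3 to 0.7, the simulated F test rejects in 40% to 81% of trials at d = 0.4 and 60% to 95% at d = 0.5.

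**Chi-square, if run across all three arms.** With assumed rates of BDI ≥20 of 10%, 10% and 20% (AA, SAA, control), it rejects in about 32% (52 per arm) or 39% (65 per arm).

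**Power of the direct contrast.** The noncentrality is d × √(n/2). At 0.8 SD and 52 per arm it is 0.8 × √26 = 4.08, giving 98% power (96% at alpha 0.025). At 0.4 SD it is 2.04, giving 52%. With 65 per arm it is 0.4 × √32.5 = 2.28, giving 62%.

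**The case against.** The strongest reply is that this is a condensed article listing families of tests. Pairwise comparisons after ANOVA are routinely left to the full protocol or analysis plan, neither of which is shown. The closing sentence of 2.9.1 also covers the within-group paired t-tests, so it may be a general statement of purpose and not a decision rule. It is true that follow-up contrasts may exist elsewhere. But the article goes beyond leaving them out: it names the test, the threshold and the conclusion that the comparisons support. For ANOVA, that conclusion is attached to a test that cannot deliver it.

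Some stronger readings are tempting and should be resisted:

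- **Every stated test is a three-arm omnibus test.** Only ANOVA and the time-by-group interaction clearly are. The text does not say how many arms enter the chi-square or rank-sum tests, and the interaction is in 2.9.2, after the sentence about therapeutic effects, so its role as evidence for AA is inferred from context.
- **ANOVA rejects whenever AA equals sham.** It rejects with a probability that depends on an assumed shared benefit. At 0.2 to 0.3 SD with 52 per arm it usually does not.
- **The sham arm contributes nothing.** Means and SDs will be presented, so a close match between AA and SAA would be visible. The flaw is in the inference, not the data.
- **Control participants are unblinded.** The text does not say so; this is inferred from education-only care and from masking steps limited to AA and SAA.

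Two further objections stand in part. SAA participants press tape at the same points, so AA minus SAA isolates the seeds; it is the contrast for superiority over sham, not a complete account of every component of acupressure. And the planned 0.8 SD is tied to a drug control group, so it cannot be assumed for AA versus SAA.

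**Conclusion.** The concern holds for the named ANOVA. Followed as written, the plan evaluates AA with a test whose significance does not show that AA is better than sham, and it names no contrast that would. With AA and SAA identical and a shared benefit over control of 0.2 to 0.8 SD, the chance of a significant result is 17% to 99% with 52 per arm and 20% to 99.8% with 65, against 5% for the direct contrast. These rates rest on normal outcomes with equal SDs and on an assumed shared benefit that the document does not quantify. The interaction test shares the property, as would chi-square and rank-sum tests if they span all three arms. The article does not establish that pairwise tests are excluded, nor that a false claim would follow; the finding is that its wording permits one.

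**What to change.** In 2.9.1 and 2.9.2, name two contrasts from the same models, AA minus SAA and AA minus control, each with an estimate and 95% CI. For BDI ≥20, give pairwise risk differences for the same two contrasts. State that:

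- any claim that AA is better than sham rests on AA minus SAA;
- AA minus control is the effect of the whole package, including attention and expectation;
- the omnibus test alone supports no efficacy statement.

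Say explicitly which arms enter the chi-square and rank-sum tests.

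This changes wording and adds two contrast statements; it needs no new data. It is not free in power. The 98% for AA versus SAA with 52 per arm depends on the full 0.8 SD applying to that contrast. At half that effect, power is about 52% (62% with 65), so a positive result may be limited to AA versus control. The sponsor should record this before unblinding.
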